# Comprehensive Travel Health Education for Tour Guides: Protocol for an Exploratory Sequential Mixed Methods Research

**DOI:** 10.2196/33840

**Published:** 2022-05-23

**Keywords:** travel health, health education, tour guides, tourists, health promotion

## Abstract

**Background:**

Tourists are at risk of experiencing health problems during their travel. However, even though tour guides have the potential to become travel health promoters, their participation has not been optimal.

**Objective:**

This study aims to develop a comprehensive travel health education model to help tour guides improve health information delivery to tourists.

**Methods:**

This is an exploratory sequential mixed methods research. The first phase consisted of a qualitative study with an informed grounded theory design. In-depth interviews were carried out with tour guides from all language divisions and policymakers of the Indonesian Tour Guide Association Bali Branch or Himpunan Pramuwisata Indonesia Daerah Bali (HPI Bali). The interview guidelines were developed based on the theory of planned behavior and identity theory. Qualitative data were analyzed thematically. In the interim phase, a travel health education model and questionnaire were developed based on the qualitative findings. The initial model and its instruments were finetuned after consultation with travel medicine and health promotion experts. Furthermore, the validity and reliability of the questionnaire were tested on 30 tour guides. The second phase consisted of a quantitative study with a randomized pretest-posttest control group design. A total of 76 tour guides in the intervention group received comprehensive travel health education, while 76 in the control group received no specific intervention. Outcome variables (ie, attitudes, subjective norms, perceived behavioral control, actual behavioral control, role identity, and behavioral intention) were measured at baseline (T_0_), after the online training (T_1_), before information sharing via WhatsApp (T_2_), a month after the start of the WhatsApp intervention (T_3_), and at the end of the WhatsApp intervention (T_4_). The mean difference of each outcome variable before and after the intervention will be compared between the intervention and control groups. Thereafter, the quantitative and qualitative findings will be integrated into a joint display.

**Results:**

The qualitative phase was conducted through in-depth interviews with 21 informants who included tour guides and policymakers from HPI Bali from May to June 2021. The education model, educational materials, and questionnaire were developed based on the qualitative findings and consultation with experts. The education model consists of online training and information sharing through WhatsApp and was trialed with tour guides from November 2021 to February 2022. As of April 2022, this study is in the quantitative data analysis stage.

**Conclusions:**

A travel health education model was developed based on qualitative findings and consultation with experts. The model was tested with tour guides, and a series of self-administered questionnaires were completed. This study is in the quantitative data analysis stage and will continue by integrating qualitative and quantitative findings into a joint display.

**Trial Registration:**

ClinicalTrials.gov NCT04961983; https://clinicaltrials.gov/ct2/show/NCT04961983

## Introduction

### Background

Tourists are an epidemiologically important population because they are potentially exposed to diseases outside their home country and may serve as a conduit for diseases from their origin to destination country or vice versa [1]. Tourists visiting tropical, subtropical, and developing countries, including Indonesia, are at a higher risk of morbidities and mortalities due to the lack of hygiene, sanitation, safety, and disease endemicity of the destinations [2-5].

Several studies in Australia revealed less than optimal pretravel health behavior of tourists visiting Southeast Asia, including Indonesia. There were low proportions of tourists seeking pretravel consultation, receiving malaria chemoprophylaxis, and receiving a vaccination for typhoid and hepatitis B [6-8]. According to the literature, health problems that tourists experience during their visits to Indonesia include diarrhea, tropical infections (eg, dengue hemorrhagic fever, typhoid, malaria), respiratory infections (including COVID-19), animal bites (ie, rabies), methanol intoxication, and injuries or trauma due to accidents in tourism sites or traffic accidents [3,9-17]. Mapping of safety hazards and risks based on the World Health Organization (WHO) criteria for 197 tourist attractions in Bali concludes that 6.6% are high-risk areas, 39.1% are moderate risk, and the rest are low risk [14,15].

These facts indicate that tourists need local, specific, and up-to-date information on the prevention of travel-related health problems to adopt appropriate prevention measures. A tour guide is one actor in the tourism industry that potentially delivers health information to tourists due to their intensive contact with tourists during their visits [18-20]. As one of the best-known tourism destinations in the world, Bali is a province with the highest number of international tourist visits in Indonesia [21]. Bali has a great potential to involve tour guides in travel health promotion because it boasts 5470 registered tour guides, which is more than half of the total number of tour guides in Indonesia [22]. However, a cross-sectional study in Bali suggested that about half of the tour guides in Bali never or rarely provide health information to the tourists they serve [23]. This indicates the need for improved tour guide behavior and a need to address its determinants, namely attitude, subjective norms, role identity, self-efficacy, and knowledge [23].

There is no published literature to date on interventions to improve tour guides’ involvement in travel health promotion. Therefore, a comprehensive, relevant, and effective intervention addressing determinants of tour guides’ behavior in providing travel health information should be developed. Accordingly, this study aims to develop a comprehensive travel health education intervention relevant to the needs of tour guides providing travel health information to tourists in Bali. In addition, this study aims to assess the efficacy of the intervention to improve tour guides’ attitude, subjective norms, perceived behavioral control, actual behavior control, role identity, and intention to provide information regarding the prevention of travel health problems.

### Theoretical Foundation

An integration of the theory of planned behavior (TPB) and identity theory was employed as the reference for developing the intervention because the constructs of these theories are relevant to the determinants of tour guides’ behavior in travel health promotion [23-26]. TPB purports that human behavior is determined by three types of considerations: behavioral beliefs, normative beliefs, and control beliefs. Each of these beliefs will shape attitudes toward behavior, subjective norms, and perceived behavioral control, which in turn will affect behavioral intention. Behavioral intention and actual behavior control will ultimately determine the implementation of a particular behavior [26,27].

TPB has been used extensively in the development of behavior change interventions in the last three decades, including in the health sector [28-30]. TPB is used in this study because the delivery of travel health information by tour guides is a planned and voluntary behavior influenced by both internal and external determinants. There are limited publications related to the application of TPB in interventions to change actors’ individual behavior to become health promoters with the primary purpose of changing the health behavior of others [29,30]. The application of TPB to interventions that target nonhealth actors to make them health promoters in the context of travel health is even less explored, calling for further study [31].

A tour guide’s role as a nonhealth actor is a determinant that can influence their health-promoting behavior. Therefore, this research proposes an extended TPB by integrating identity theory into TPB [28]. The travel health education model developed in this study is a comprehensive intervention as it targets all determinants of health behavior based on the construct of extended TPB.

## Methods

### Trial Registration

This study was registered in ClinicalTrials.gov (NCT04961983).

### Study Design

This research employs an exploratory sequential mixed methods design, in which the collection and analysis of qualitative data are conducted prior to the quantitative data [32,33]. The qualitative study results in the first phase became the basis for the intervention development in the interim phase. The intervention was then tested for its efficacy in the quantitative study. The workflow is presented in Figure 1.

**Figure 1 figure1:**
[figure not shown]
Workflow of an exploratory sequential mixed methods study to develop a travel health education model.

### Study Setting and Population

This study was conducted in Bali, Indonesia. The study population comprised of 5470 tour guides who are registered members of the Indonesian Tour Guide Association Bali Branch or Himpunan Pramuwisata Indonesia Daerah Bali (HPI Bali).

### Phase 1: Qualitative Study

#### Study Design

The first phase of this research consisted of a qualitative study with an informed grounded theory, a design in which processes and products are developed in accordance with grounded theory but informed by existing theoretical frameworks [34].

#### Informants

At the beginning of this study, purposive sampling was employed, a nonrandom method ensuring that particular categories of informants within the population were represented in the study [35]. Informants were recruited based on the category of language division. There are 11 language divisions in HPI Bali: English, Japanese, Korean, Mandarin, France, Dutch, Italian, Spanish, Russian, German, and Indonesian. Every language division in HPI Bali has its own market countries (eg, tour guides in the English language division serve tourists from English-speaking countries). Therefore, 11 tour guides from all language divisions of HPI Bali were interviewed to gain a comprehensive understanding of the health education needs of tour guides serving tourists from various countries. In addition to the tour guides, we conducted in-depth interviews with 2 policymakers from HPI Bali to explore more perspectives regarding a feasible and relevant travel health education model to address tour guides' needs. Based on the ongoing data analysis results, 8 tour guide informants were recruited using theoretical sampling, recruitment based on data that require further exploration [35]. These informants were recruited through HPI Bali or snowballed from the previously interviewed informants. The prospective informants received an explanation of the research, and those who were willing to participate were asked to provide written consent.

#### Interview Guides

Questions for the semistructured interview guide were developed with reference to the constructs of the TPB, which was integrated with the identity theory. The interviews explored the following themes:

Health problems experienced by tourists during their visitAttitude, subjective norms, perceived behavior control, role identity, actual behavioral control, and intention to provide information regarding travel healthProvision of travel health information to tourists and barriers faced in conveying the informationTour guides’ needs for travel health informationEducational strategies pertinent to tour guides’ needs (content, mode of delivery, duration, setting, supporting facilities)

All topics were explored through open questions. The order of questions was flexible according to each informant's response during interviews. Other information outside the interview guide that was interesting and important was also explored by the interviewers.

#### Data Collection

Data collection was carried out in person following COVID-19 health measures (ie, wearing masks and physical distancing) in the place and time agreed by the informant and interviewer. Interviews were audio recorded with the informants’ consent. Data collection and analysis were conducted concurrently. Recruitment of informants were stopped when the data reach theoretical saturation, the point at which no new theoretical insight emerges [35].

#### Data Analysis

The qualitative data were analyzed using inductive thematic analysis, in which the researcher identifies patterned themes [36]. Thematic analysis steps include interview transcription, familiarization of data, open coding of the entire data, axial coding (identifying the association of codes and integrating associated codes into a thematic category), selective coding (selecting and integrating categories into main themes to construct a theory), and report writing. The report also contained a joint display to link the qualitative findings with the detailed components of intervention design. Strategies to increase the trustworthiness of the research findings included triangulation of sources and peer debriefing with experts in travel health and health promotion [33]*.* NVivo 12 Plus software was utilized in the data analysis process.

### Interim Phase

In the interim phase, the qualitative findings were used to develop an intervention in the form of a travel health education model and its instruments (ie, travel health promotion guidebook for tour guides, training module, and media for WhatsApp information sharing), as well as a questionnaire to be tested in the quantitative study. The integrative procedure in this study was represented in a joint display. Joint display explicitly presents how the codes and themes that emerged in qualitative research have shaped the intervention elements [32]. The initial education model, its instruments, and the questionnaire were refined after consultation with travel medicine, health promotion, and tour guiding experts who provided input regarding the content and delivery formats. The questionnaire then underwent a pilot test on 30 tour guides. The validity and reliability of the questionnaire were analyzed, and revisions were made accordingly.

### Phase 2: Quantitative Study

#### Study Design

The research then continued with a quantitative strand using an experimental randomized pretest-posttest control group design. The intervention group received intervention in the form of a comprehensive travel health education model, while the control group received no intervention but standard health information provision.

#### Participants

The minimum sample size in this study was calculated by employing the WHO Sample Size Determination software using the formula of a 1-tailed hypothesis test for a difference in two population means [37]. Using the parameters *d*=10.0, µ1=71.2, µ2=66.2, α=.05, and 1–β= 90% and taking into account a dropout rate of 10%, the minimum number of samples for each intervention and control group was 76. Sample selection was carried out with disproportionate stratified random sampling from the list of tour guides who were HPI Bali members. The selected tour guides were contacted to determine if they met the eligibility criteria. Those who did were given a further explanation of the research and asked to sign the informed consent form if they were willing to participate.

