#### Study Outcomes

The outcomes of this study referred to the constructs of integrated TPB and identity theory, including attitude, subjective norms, perceived behavioral control, actual behavioral control, behavioral intention, and role identity. A summary of the outcomes is presented in Table 1.

In addition to those outcome variables, several variables were controlled by analysis, namely age, sex, education, length of work, employment status, tourists’ country of origin, and type of tourism activities.

**Table 1 table1:** Summary of study outcomes.

Study outcomes	Definition	Data measurement and analysis scale	Data source (time point)
Attitude	Psychological tendencies expressed by the tour guides regarding providing travel health information to tourists	Measurement scale: ordinal (Likert scale) Data analysis scale: interval	Self-administered questionnaire (T_0_, T_1_, T_2,_ T_3,_ T_4_)
Subjective norms	Tour guides’ perception of the extent to which providing travel health information to tourists is something that is expected by the tourists they serve, their employers (travel agents), HPI^a^, and the community	Measurement scale: ordinal (Likert scale) Data analysis scale: interval	Self-administered questionnaire (T_0_, T_1_, T_2,_ T_3,_ T_4_)
Perceived behavioral control	Tour guides' confidence in their ability to provide travel health information to tourists	Measurement scale: ordinal (Likert scale) Data analysis scale: interval	Self-administered questionnaire (T_0_, T_1_, T_2,_ T_3,_ T_4_)
Actual behavioral control	Tour guides’ knowledge regarding the prevention and first aid of travel health problems	Measurement scale: ordinal (Likert scale) Data analysis scale: interval	Self-administered questionnaire (T_0_, T_1_, T_2,_ T_3,_ T_4_)
Role identity	Tour guides’ perception of the extent to which travel health promotion is a part of their role	Measurement scale: ordinal (Likert scale) Data analysis scale: interval	Self-administered questionnaire (T_0_, T_1_, T_2,_ T_3,_ T_4_)
Behavioral intention	Tour guides’ willingness to provide travel health information to the tourists they serve	Measurement scale: ordinal (Likert scale) Data analysis scale: interval	Self-administered questionnaire (T_0_, T_1_, T_2,_ T_3,_ T_4_)

^a^HPI: Himpunan Pramuwisata Indonesia (Indonesian Tour Guide Association).

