#### Data Management and Analysis

Quantitative data were extracted from the digital questionnaires and transferred to the database. Coding was done to the extracted data, and data values were checked by two data analysts. Data without participants’ names were exported into a file format suitable for analysis with statistical software. The electronic data were stored on a computer protected with a password and only accessible to the research team.

Quantitative data will be analyzed descriptively by calculating the frequency distribution for categorical data as well as the total scores, mean, median, standard deviation, and range of minimum to maximum scores on numerical data. The comparability of the intervention group and the control group in terms of control variables will be analyzed using the chi-square test for categorical data and independent *t* test or Mann-Whitney *U* test for numerical data [39-41]. Data normality will be calculated using Kolmogorov-Smirnov test. Additionally, data homogeneity will be tested using the Levene test [39,42]. A complete case analysis will be performed to handle missing outcome data.

The mean comparison test will be conducted to determine mean differences between the intervention and the comparison groups. Repeated measures analysis of covariance (ANCOVA) will be employed because the measurement of dependent variables was conducted repeatedly at 5 time points, and there are covariates that need to be controlled in the analysis [39].

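### The 90% power behind 76 per group comes from a 1-tailed 5% test, and the repeated measures ANCOVA named for the analysis is not declared one-tailed, so the 90% is not supported for it

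*Protocol article*

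**What the plan says.** The Participants section (Methods, Phase 2) describes the sample size calculation as done "using the formula of a 1-tailed hypothesis test for a difference in two population means". Its inputs are d="10.0, µ1=71.2, µ2=66.2, α=.05, and 1–β= 90"%. The symbol d is not defined. The result is given as "taking into account a dropout rate of 10%, the minimum number of samples for each intervention and control group was 76".

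The Data Management and Analysis section describes the comparison as follows: "The mean comparison test will be conducted to determine mean differences between the intervention and the comparison groups". It then names the model: "Repeated measures analysis of covariance (ANCOVA) will be employed because the measurement of dependent variables was conducted repeatedly at 5 time points". The Study Outcomes section lists the control variables: "several variables were controlled by analysis, namely age, sex, education, length of work, employment status", followed by tourists' country of origin and type of tourism activities. The baseline score is not on that list; T0 is one of the five repeated measurements. Missing outcome data are to be handled by complete case analysis.

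The analysis section gives no direction, sidedness or significance level for the ANCOVA. The Introduction frames the aim as improvement. The Results and Discussion report that the 76 in each group took part to the end.

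**The concern.** The critical value used for sizing and the one the named analysis would apply by default are different. An ANCOVA F test with one numerator degree of freedom (the overall group effect) is equivalent to a two-sided t test. A group-by-time F test over five time points has (2-1)×(5-1)=4 numerator degrees of freedom and has no one-tailed form. A power figure computed at the one-tailed 5% point does not carry over to either.

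Two consequences follow if this is left open. A non-significant F test would be read against a claimed false-negative risk of 10%, a figure not derived for that test. Or a one-sided p-value at .05 could be reported by pointing back to the sample size section. That allows a 5% chance of a false claim of benefit, against 2.5% in that direction under a two-sided 5% test.

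**Working it through.** **Inputs.** From Participants: means 71.2 and 66.2, so the difference is 5.0; alpha .05; power 90%; dropout 10%; 76 per group. Assumption: d=10.0 is the common SD.

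**Step 1: reproduce the plan's figure.** For two means with equal allocation, n per group = 2·SD²·(z_alpha + z_beta)²/difference².

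- One-tailed 5%: 2×100×(1.645+1.2816)²/25 = 68.5, so 69. With the dropout allowance, 69×1.1 = 75.9, so 76. This matches the stated number and supports reading d as the SD.
- Two-sided 5%: 2×100×(1.960+1.2816)²/25 = 84.06, so 85. With 10% loss, 85/0.9 = 94.4, so 95. This does not reproduce 76.

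The stated 76 at 90% power therefore depends on the one-tailed choice.

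**Step 2: power at the stated size.** Unadjusted comparison of two means, difference 5, SD 10, noncentral t with 2n-2 degrees of freedom and noncentrality 5/(10·√(2/n)). The 68 is 76×0.9 = 68.4, rounded down.

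| Analysed per arm | One-tailed 5% | Two-sided 5% |
|---|---|---|
| 68 (planned 10% loss) | 89.5% | 82.5% |
| 76 (no loss, as reported) | 92.3% | 86.5% |

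The normal approximation gives 83.0% and 86.9% for the two-sided column. The two-sided false-negative risk is thus about 13.5% with 76 per arm, or 17.5% with 68.

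**Step 3: what covariates could add.** Suppose the covariates together correlate rho with the outcome at a single time point, so that the residual SD is 10·√(1-rho²). The document gives no value of rho, so a range is shown (two-sided 5%, noncentral t).

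| rho (assumed) | 68 per arm | 76 per arm |
|---|---|---|
| 0 | 82.5% | 86.5% |
| 0.2 | 84.0% | 87.8% |
| 0.3 | 85.9% | 89.4% |
| 0.4 | 88.5% | 91.6% |

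On this basis 90% is reached at rho of about 0.33 with 76 per arm (0.33² = 11% of outcome variance explained) and about 0.45 with 68 per arm (0.45² = 20%).

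Step 3 is still a one-time-point contrast. The power of the full repeated measures model also depends on the correlations between time points and on which effect (group, or group by time) carries the conclusion. The document supplies neither, so that power cannot be computed from it.

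**The case against.** The strongest reply is that the document does not contradict itself on sidedness. The only sidedness it states is one-tailed, the aim is directional, a single-degree-of-freedom group contrast from an ANCOVA can be tested one-sided, and such detail is often left to an analysis plan that is not shown. Part of this stands: the two-sided reading of the analysis is inferred from the named method, not stated. But the article gives the sidedness, alpha, power and size of one test and then names a test of another form. A directional aim does not make an F test one-tailed, and the group-by-time F test cannot be made so.

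A reader might also infer that the planned ANCOVA has only 82-83% power, so that the promised 90% is shown not to be delivered. The document does not support this, for two reasons.

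- The 82-83% belongs to an unadjusted two-sample comparison. The covariate-adjusted model could reach 90%, as Step 3 shows. Equally, no gain can be claimed: the sample size section takes no credit for covariates, the baseline score is not among those listed, and no correlation is given.
- It assumes the planned dropout. The article reports full participation in both groups, so about 86% is the unadjusted figure that applies.

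Finally, data collection was complete when the article was written, so restating the power cannot change the sample. This is true, but analysis was still under way as of April 2022, and the restatement bears on how a null result, or a one-sided p-value, would be read.

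**Conclusion.** The concern holds in a limited form. The stated 90% rests on a one-tailed 5% comparison of two means and is not supported for the repeated measures ANCOVA that the analysis section names. Under a two-sided 5% test without credit for covariates, power for a 5-point difference is about 86% with 76 per arm analysed, and about 82-83% after the planned loss. The shortfall is 3 to 4 percentage points on the participation reported and 7 to 8 as planned.

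This rests on two assumptions: that d=10.0 is the SD, which the exact match to 76 supports, and that the F tests are read in their usual non-directional way. It does not establish that the adjusted model falls below 90%; that is unknown. The sample size arithmetic, taken as a one-tailed calculation, reproduces. What needs correcting is the link between that calculation and the analysis.

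**What to change.** Keep 76 per arm and make two changes.

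- In Data Management and Analysis, state that group comparisons are two-sided at the .05 level.
- In Participants, define d as the SD if that is what it is, and restate the power: for an unadjusted 5-point difference, 76 per arm gives about 86% two-sided power at .05, or about 82-83% after 10% loss. If a gain from covariates is mentioned, give it as a range over assumed correlations, as in Step 3, and label it an assumption. A single favourable value should not be quoted.

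The cost is a sentence in each section and a slightly less favourable power figure. No participants are added and the model does not change.
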